#### Preliminary Efficacy

Although this investigation is mainly focused on optimizing adherence and retention to the intervention, we will conduct analyses examining the preliminary efficacy of the intervention. Our primary measures of preliminary efficacy will be depressive symptom severity, as assessed by the PHQ-8 [55]. We will also assess change in positive and negative emotion and other indicators of psychological adjustment (eg, perceived stress and meaning and purpose) as secondary outcomes.

For each outcome, we will estimate growth curves within a multilevel modeling (MLM) framework [97] to assess change in each outcome across the four assessment points (baseline, post intervention, FU1, and FU2). MLM offers an approach that accommodates missing data points and nonindependence in observations. We plan to model time at level 1 and randomization arm at level 2 using dummy variables to represent each arm. In phase 1, the primary parameters of interest will be the differences in the magnitude of change in preliminary efficacy outcomes between the intervention arm and each of the control arms over time. In phase 2, the primary parameters of interest will be the magnitude of change in outcomes across all three randomization arms over time. In phase 2, we will also explore whether the three enhancement arms (facilitator contact, ODB, and virtual badges) differ in their magnitude of change in preliminary efficacy outcomes over time. In phase 3, the primary parameter of interest will be the difference in the magnitude of change in preliminary efficacy outcomes over time for the arms that received the intervention relative to the emotion-reporting control. In phase 3, we will also explore whether there are differences in the magnitude of change in outcomes over time as a function of enhancement type (no enhancement, facilitator contact, ODB, or virtual badges), as well as whether receiving certain combinations of enhancements may influence magnitude of change in outcomes over time. We will use significance tests comparing the information criteria of different models to determine which covariates to include in the final model.

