#### Assessments and Incentives

For all three pilot trials (phases 1-3), we are administering assessments at the following four time points (see Figure 1): baseline, post intervention (7 weeks post baseline), follow-up 1 (FU1; 1 month post intervention), and follow-up 2 (FU2; 3 months post intervention). The EMA text distribution and data collection are administered using PingQuest [60], a platform for the delivery and management of ecological momentary assessment data, developed by one of the authors (MC). All other assessments are administered online. In phase 1, we are using Qualtrics survey software [61] for Web-based data collection and management. In phases 2 and 3, we are using REDCap [62] for Web-based data collection and management, hosted at Northwestern University. Both Qualtrics and REDCap are secure, Health Insurance Portability and Accountability Act of 1996 compliant, Web-based apps designed to support data collection and management for research studies. Participants for all three pilot trials are compensated up to US $60 total: US $45 for completion of all assessments (US $5 for baseline, US $20 for post intervention, and US $10 for each follow-up) and up to US $15 for completing the first 3 weeks of daily website visits or completing the intervention [35,55,56,63].

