**Session 5**		
	Skill 8: acts of kindness	Engaging in small acts of kindness can help promote happiness and well-being for the individual, in addition to strengthening our relationships
	Depression material	Small, prosocial acts that can be performed even if one is relatively socially isolated
	Exercises	Do something nice for someone else each day and record it in a daily kindness journal

^a^MARIGOLD: Mobile Affect Regulation Intervention with the Goal of Lowering Depression.

The skills are (in the order that they are presented) as follows: (1) noticing positive events, (2) amplifying positive events, (3) gratitude, (4) behavioral activation, (5) mindfulness, (6) positive reappraisal, (7) personal strengths, and (8) acts of kindness. MARIGOLD is delivered as a self-paced, Web-based intervention arranged into five modules containing 1 to 3 skills each. Each module is designed to be completed within 1 week; however, to allow for variations in individual schedules and self-pacing, participants are given a total of 7 weeks to complete the MARIGOLD course. Participants must finish the current week’s skills before the next one’s become available, so the skills are taught in succession. Each skill is associated with a home practice exercise in a journal format, and participants are encouraged to spend approximately 10 min each day reviewing the skill and completing home practice. Participants may also revisit previous weeks’ skills and home practice exercises. After completion of the course, participants maintain access to the course website indefinitely, allowing them to review the skills or continue with their home practice.

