In addition, booster sessions that contain brief summaries of the positive emotion skills, along with encouragement and goal setting for continued practice, become available immediately after course completion. For example, if participants are going through a booster session for skill # 8: acts of kindness, they will review a brief summary the skill, as well as a few examples of random acts of kindness. They will also have the chance to review their previous journal entries for the skill and print out a bonus handout on the skill. Finally, in the booster sessions, participants have the opportunity to set a goal to enact the skill. Specifically, participants will be asked to complete the following steps: (1) set a goal for enacting the skill (ie, “I will commit to doing something nice for a friend, loved one, or stranger every day”), (2) a time frame of the commitment (1 week, 2 weeks, 1 month, or 2 months), (3) the frequency of the commitment (more than once a day, once a day, every other day etc), (4) how they plan to keep track of their commitment (write about it on the MARIGOLD website or talk to a friend or activity partner), (5) write down an encouraging note to themselves for when it gets difficult to enact the skill, and (6) digitally sign their name to a summarized page with their commitment. Following these six steps, participants will be emailed a copy of their responses as a reminder.

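### In phases 1 and 3 the efficacy parameter is an arm difference in change over time with no named time point or shape of time, and phase 1 keeps FU2 in it after controls have received the intervention

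*Protocol article*

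**What the plan says.** Under Preliminary Efficacy the article states, of all its efficacy measures, that "we will estimate growth curves within a multilevel modeling (MLM) framework [97] to assess change in each outcome across the four assessment points". The model terms are given as "We plan to model time at level 1 and randomization arm at level 2 using dummy variables to represent each arm". For phase 1 the parameters of interest are "the differences in the magnitude of change in preliminary efficacy outcomes between the intervention arm and each of the control arms over time". For phase 3 there is one: "In phase 3, the primary parameter of interest will be the difference in the magnitude of change in preliminary efficacy outcomes over time", comparing the arms that received the intervention with the emotion-reporting control. No time point is attached to either, and nothing says whether time is linear, curved, piecewise or categorical.

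Assessments and Incentives sets the schedule as "baseline, post intervention (7 weeks post baseline), follow-up 1 (FU1; 1 month post intervention), and follow-up 2 (FU2; 3 months post intervention"). On the course itself, "participants are given a total of 7 weeks to complete the MARIGOLD course". After it, "participants maintain access to the course website indefinitely, allowing them to review the skills or continue with their home practice", and booster sessions "become available immediately after course completion".

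The Phase 1 section adds that both control arms are given the MARIGOLD intervention once they have completed FU1. Preliminary Efficacy does not exempt FU2 from the phase 1 comparison.

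**The concern.** The taught course is over by week 7, but the analysed period runs to about week 20. A between-arm effect that appears by week 7 and then holds, or partly fades, is not a straight line through the four assessments. If the single difference in change over time is an arm-by-time slope, it answers a different question from whether participants were better off when the course ended. The two questions can have very different answers on the same data. The primary efficacy outcome (PHQ-8) and all secondary efficacy outcomes share this definition.

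Phase 1 has a further difficulty that needs no assumption about natural fading. Once controls have the intervention, the arms can converge at FU2 even though the intervention arm has lost nothing.

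**Working it through.** The article gives no power or sample-size figure for efficacy, so there is none to reproduce.

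**Inputs from the article.** Assessments at t = 0, 7, 11.35 and 20.04 weeks (one month = 4.35 weeks). Phase 3: 600 in nine arms, so 600/9 = 66.7 controls and 533.3 in the eight intervention arms.

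**Assumptions, not in the article.** Linear time; complete data; SD 1 at each assessment; equal correlation 0.5; week-7 effect d = 0.36 SD; two-sided alpha 0.05; normal approximation. Benefit is counted as positive.

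**Slope.** With mean t = 9.60, the weights t − mean are −9.60, −2.60, +1.75, +10.45, and their sum of squares is 211.1. The slope is Σ(weight × arm difference)/211.1.

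| Arm difference at the four assessments | Slope per week | Slope × 20.04 |
|---|---|---|
| Maintained (0, d, d, d) | 9.60d/211.1 = 0.0455d | 0.91d |
| Fading (0, d, 0.7d, 0.4d) | (−2.60 + 1.22 + 4.18)d/211.1 = 0.0133d | 0.27d |
| Phase 1, controls catch up fully by FU2 (0, d, d, 0) | (−2.60 + 1.75)d/211.1 = −0.0040d | −0.08d |
| Phase 1, controls catch up halfway (0, d, d, 0.5d) | (−2.60 + 1.75 + 5.22)d/211.1 = 0.0207d | 0.41d |

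The fading slope is 0.0133/0.0455 = 29% of the maintained one.

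**Power in phase 3.** Let f = 1/533.3 + 1/66.7 = 0.01687. Power is Φ(effect/SE − 1.96).

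- Slope: SE = √(0.5/211.1 × f) = 0.00632. Maintained: 0.36 × 0.0455/0.00632 = 2.59, power 74%. Fading: 0.36 × 0.0133/0.00632 = 0.76, power 11%.
- Week-7 change from baseline: SE = √(2 × 0.5 × f) = 0.130. 0.36/0.130 = 2.77, power 79% under either pattern.
- Week-7 contrast with baseline constrained equal: SE = √((1 − 0.5²) × f) = 0.1125. 0.36/0.1125 = 3.20, power 89% under either pattern.
- Slope with baseline constrained equal (arm difference = b·t): the generalised least squares b is 0.0539d if maintained and 0.0240d if fading, with SE = √(f/569.5) = 0.00544, where 569.5 = 2[Σt² − 0.2(Σt)²]. The ratios are 3.57 and 1.59, so power is 95% and 35.5% (about 36%).

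**Sensitivity to the shape of time.** In the same fading case, without the baseline constraint, the fitted week-7 change has about 82% power with a knot at week 7 (recovering 0.96d) and about 74% with a quadratic (recovering 0.73d).

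**Phase 1 timing.** From FU1 to FU2 is 20.04 − 11.35 = 8.7 weeks, longer than the 7 weeks allowed for the course. Controls therefore have time to complete it before FU2.

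**The case against.** The strongest reply is that the article never says linear or slope. A growth curve may be quadratic or piecewise, and either would keep most of the week-7 effect visible. The shape of time, the covariance structure and the exact contrast are usually left to an analysis plan, and this is a condensed article. That stands. A reader might infer that the plan will miss a real effect; the text does not support this, because the loss belongs to one possible choice of model.

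Other tempting inferences also go too far:

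- That treatment stops at week 7. The taught course does, but site access and boosters continue, and the Introduction describes long-lasting effects of similar interventions. The 0.7d and 0.4d fade is an illustration, not a figure from the article, though Strengths and Limitations does leave longer persistence as an open question.
- That uneven spacing is the cause. Coding the assessments 0 to 3 gives nearly the same results.
- That the fitted line shows only 0.32d at week 7 when the effect is maintained. That is slope × 7 and leaves out the fitted intercept difference of 0.31d; the line itself shows about 0.63d.
- That a slope is always worse. With baseline constrained equal in both analyses, it beats the week-7 contrast when the effect is maintained (95% v 89%).

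What remains is that the headline parameter is stated here and is compatible with estimands that can disagree sharply. The phase 1 difficulty rests on the article's own design and not on an assumed natural decay.

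**Conclusion.** The point holds for phases 1 and 3, in a conditional form for phase 3. The parameter is not tied to a time point, and its meaning depends on an unstated shape of time. Under linear time and a fade to 0.7d and 0.4d, power falls to about 11% (36% constrained) against 79% (89%) at week 7. If the effect is maintained, the unconstrained gap is small (74% v 79%) and the constrained slope is slightly ahead. These figures rest on the assumed d, correlation, complete data and decay pattern.

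In phase 1, FU2 is not a comparison with untreated controls whatever the shape of time. If controls catch up fully, a lasting benefit gives a linear slope of about −0.08d over 20 weeks: essentially nothing, with the sign slightly reversed. Full catch-up is an assumption; catching up halfway leaves 0.41d against 0.91d.

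Phase 2's primary parameter is change across three intervention arms with no untreated control, and it is not affected.

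**What to change.** In Preliminary Efficacy:

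1. Fit assessment as a categorical factor, or a growth curve with a knot at week 7, with baseline means constrained equal across randomised arms.
2. Name the arm difference at post intervention (week 7) as the headline contrast, with the FU1 and FU2 differences as maintenance contrasts.
3. For phase 1, limit the between-arm comparison to assessments up to FU1. FU2 can still be described within arms.

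This changes analysis wording only; no new data are needed. The cost is a few more parameters, no single slope to quote, and slightly less power than a baseline-constrained slope if the effect is fully maintained (89% v 95% under the assumptions above).

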#### Randomization

In phase 1, participants are randomly assigned to one of the three groups using simple randomization. In phases 2 and 3, we are stratifying randomization based on gender and level of depressive symptom severity to ensure sufficient numbers of each group within each condition. We are using the 8-item Patient Health Questionnaire (PHQ-8) [55] as our measure of depressive symptom severity. In phase 2, we are stratifying based on three levels of depressive symptom severity (PHQ-8 score: 5-9, mild; 10-14, moderate; ≥15, severe) [55] and by gender. However, to be more consistent with recommended interpretations of PHQ scores [59], in phase 3, we are stratifying based on four levels of depressive symptom severity (PHQ-8 score: 5-9, mild; 10-14, moderate; 15-19, moderately severe; ≥20, severe) and by gender. The randomization assignments were computer-generated via the study survey software (Qualtrics in phase 1 and Research Electronic Data Capture, REDCap in phases 2 and 3) that accounted for participants’ demographic information and depressive symptom severity scores. The computer-generated randomization was performed by the study coordinator, who was not involved with either the intervention or the assessments, as both were completed online.

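### The efficacy growth curves set no common baseline mean across arms; fitting one would sharpen the phase 1 and phase 3 contrasts at no cost in data

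*Protocol article*

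**What the plan says.** The Preliminary Efficacy section of the protocol article plans multilevel growth curves for the 8-item Patient Health Questionnaire (PHQ-8) and each secondary outcome, "to assess change in each outcome across the four assessment points (baseline, post intervention, FU1, and FU2"). Baseline is therefore a modelled response. Arm enters in one sentence: "We plan to model time at level 1 and randomization arm at level 2 using dummy variables to represent each arm". The section does not say whether arm acts on the intercept, the slope or both, and it does not fix the form of time.

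The targets differ by phase:
- Phase 1: "differences in the magnitude of change in preliminary efficacy outcomes between the intervention arm and each of the control arms over time".
- Phase 3: "the primary parameter of interest will be the difference in the magnitude of change in preliminary efficacy outcomes over time", comparing all intervention arms with the emotion-reporting control.
- Phase 2: "In phase 2, the primary parameters of interest will be the magnitude of change in outcomes across all three randomization arms over time". Differences between arms are exploratory there.

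Covariates are left open: "We will use significance tests comparing the information criteria of different models to determine which covariates to include in the final model".

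The Randomization section says: "In phase 1, participants are randomly assigned to one of the three groups using simple randomization". Phases 2 and 3 stratify by gender and PHQ-8 level, with four PHQ-8 levels in phase 3. The efficacy section does not name these factors as model terms.

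**The concern.** In a standard growth curve, predictors at level 2 act on both intercept and slope. Arm dummies then give every arm its own baseline mean. Under randomisation those means are equal in the population, so the model spends information on differences known to be zero. Having baseline in the likelihood does not by itself recover the precision of a baseline-adjusted analysis while the arm intercepts are free.

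What is at stake is the width of the confidence intervals for the arm contrasts in phases 1 and 3, on PHQ-8 and on each secondary outcome. Phase 1 is small and unstratified, so chance baseline differences are largest there. In phase 3 there is a second effect on PHQ-8. If randomisation balances PHQ-8 level but the model ignores it, the reported standard error describes more variation than the design allows.

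**Working it through.** **Inputs from the protocol article.** Assessments fall at baseline, 7 weeks, and 1 and 3 months after the intervention, taken as weeks 0, 7, 11.33 and 20. Phase 3 has 600 participants in nine arms: 600/9 = 66.7, which agrees with the stated figure of about 67 per arm. Pooling eight intervention arms gives about 533 against 67. Phase 1 has 30 intervention participants against 15 in each control arm.

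**Assumptions.** The article gives no correlation, SD, effect size or power for efficacy, so there is no stated figure to reproduce. I take SD 1 at every visit, complete data and equal correlation ρ between visits (compound symmetry), with ρ from 0.3 to 0.7.

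**One time point, categorical time.** Let k = 1/n1 + 1/n0.
- Free arm intercepts: variance = 2(1 − ρ)k.
- Common baseline mean: variance = (1 − ρ²)k.
- Ratio = (1 + ρ)/2 = 0.65, 0.75, 0.85 at ρ = 0.3, 0.5, 0.7, a reduction of 35%, 25%, 15%.

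A contrast with 80% power under free intercepts has noncentrality 2.80. With a common baseline its power is Φ(2.80/√ratio − 1.96) = 94%, 90%, 86%.

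Phase 3 at ρ = 0.5: k = 1/533 + 1/67 = 0.0168. The effect detectable with 80% power is 2.80 × √0.0168 = 0.36 SD with free intercepts and 2.80 × √(0.75 × 0.0168) = 0.31 SD with a common baseline.

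**Linear slope.** With V the correlation matrix and t the visit weeks, let p = 1′V⁻¹1, q = 1′V⁻¹t and r = t′V⁻¹t. The variance of the arm difference in slope is k/(r − q²/p) with free intercepts and k/r with a common one. Under compound symmetry the ratio is S / [Σt² − ρ(Σt)²/(1 + 3ρ)], where Σt² = 577.4, (Σt)² = 1469.4 and S = 577.4 − 1469.4/4 = 210.1.
- ρ = 0.3: 210.1/345.4 = 0.61, reduction 39%.
- ρ = 0.5: 210.1/283.6 = 0.74, reduction 26%.
- ρ = 0.7: 210.1/245.6 = 0.86, reduction 14%.

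If arm enters only the slope, the plan already is the common-intercept model and the reduction is 0%.

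**Sensitivity to the covariance.** With correlation decaying over time (ρ at 7 weeks apart), the slope reductions are 54%, 46% and 32%. An uncorrelated random slope adds its variance to both sides of the ratio. At ρ = 0.5 the two terms are 0.5/283.6 = 0.00176 and 0.5/210.1 = 0.00238. An assumed slope variance of 0.001 gives 0.00276/0.00338 = 0.82, so the gain shrinks to 18%.

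**Phase 1 imbalance.** The chance baseline difference has SD √(1/30 + 1/15) = 0.32. At ρ = 0.5, an imbalance of that size shifts the change contrast by (1 − 0.5) × 0.32 = 0.16 SD.

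**Phase 3 stratification.** Suppose the strata balance a share f of the baseline PHQ-8 variance and the model omits them. The true variance is then 1 − f(1 − ρ)/2 of the reported one. At ρ = 0.5 and f = 1 this is 0.75, and a nominal 5% test has true size 2[1 − Φ(1.96/√0.75)] = 2.4%. At f = 0.8 it is 2.8%. These are limiting cases.

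**The case against.** The strongest objection is that the free arm intercept is inferred. The article names only a difference in change as its target, and arm dummies at level 2 that act on the slope alone fit the wording. A full protocol or statistical analysis plan, not shown, may settle it. This stands as a condition on the size of the loss. It does not remove the point, because the usual reading of the sentence gives the less precise model and nothing in the section rules that reading out.

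A reader might go further and infer that the plan is a raw change-score comparison that discards a quarter of the information. The documents do not support that. A slope over four visits is a weighted contrast, not a change score, even with free intercepts. The 25% needs ρ = 0.5 and a single time point, and the article states no ρ.

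A reader might also infer that the estimate is biased, from the phase 1 imbalance. It is not: that imbalance is chance variation, already counted in the standard error.

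The phase 3 figures must not be added together. The fall from 0.36 to 0.31 SD ignores stratification, while the 2.4% assumes full balance. Under full balance at ρ = 0.5, planned power would be Φ((2.80 − 1.96)/0.866) = 83% instead of 80%, and the detectable effect (0.84 × 0.866 + 1.96) × 0.130 = 0.35 SD. Full balance is unlikely with broad PHQ-8 bands across nine arms, and the article does not say whether the stratifying score is the baseline or the screening one. Balance on PHQ-8 does not automatically carry over to secondary outcomes.

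Finally, the article calls efficacy preliminary and sets no power target for it. That limits the weight of the point.

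**Conclusion.** The point holds as one of precision. On the ordinary reading of the model, the phase 1 and phase 3 efficacy contrasts are valid but wider than they need to be. With ρ between 0.3 and 0.7 and compound symmetry, a common baseline mean reduces the variance by 35% to 15% at one time point and by 39% to 14% for a linear slope. The gain is smaller with random slopes, larger if correlation decays with time, and zero if arm was always meant to enter only through change. In phase 3, the PHQ-8 standard errors may also be somewhat conservative if the strata are left out. The phase 2 primary parameter, change across all three arms, is not affected.

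**What to change.** In the phase 1 and phase 3 efficacy models, state that all arms share one baseline mean and that arm enters only through its post-baseline time terms. Use this form for PHQ-8 and for each secondary outcome. Include the phase 3 stratification factors, gender and PHQ-8 level, as fixed terms rather than leaving them to model comparison.

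If time is categorical, modelling the three post-baseline values with baseline as a covariate is a near-equivalent option. For a linear slope from baseline it is not, because a slope over weeks 7 to 20 is a different parameter; keep the constrained form there.

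The cost is a sentence or two of analysis wording and no new data, and randomisation justifies the equal-baseline assumption. The Results section reports data collection complete and analysis under way. The choice should therefore be documented as made before the arm contrasts were seen, or else the constrained model reported as a sensitivity analysis.
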